## Abstract

**Background:**

This paper details the research protocol for a study funded by the Australian Research Council. An integrated approach towards helping young children respond to the significant pressures of ‘360 degree marketing’ on their food choices, levels of active play, and sustainability consciousness via the early childhood curriculum is lacking. The overall goal of this study is to evaluate the efficacy of curriculum interventions that educators design when using a pedagogical communication strategy on children’s knowledge about healthy eating, active play and the sustainability consequences of their toy food and toy selections.

**Methods/Design:**

This cluster-randomised trial will be conducted with 300, 4 to 5 year-old children attending pre-school. Early childhood educators will develop a curriculum intervention using a pedagogical communication strategy that integrates content knowledge about healthy eating, active play and sustainability consciousness and deliver this to their pre-school class. Children will be interviewed about their knowledge of healthy eating, active play and the sustainability consequences of their food and toy selections. Parents will complete an Eating and Physical Activity Questionnaire rating their children’s food preferences, digital media viewing and physical activity habits. All measures will be administered at baseline, the end of the intervention and 6 months post intervention. Informed consent will be obtained from all parents and the pre-school classes will be allocated randomly to the intervention or wait-list control group.

**Discussion:**

This study is the first to utilise an integrated pedagogical communication strategy developed specifically for early childhood educators focusing on children’s healthy eating, active play, and sustainability consciousness. The significance of the early childhood period, for young children’s learning about healthy eating, active play and sustainability, is now unquestioned. The specific teaching and learning practices used by early childhood educators, as part of the intervention program, will incorporate a sociocultural perspective on learning; this perspective emphasises building on the play interests of children, that are experienced within the family and home context, as a basis for curriculum provision.

**Trial Registration:**

Australian New Zealand Clinical Trials Registry ACTRN12614000363684: Date registered: 07/04/2014

## Background

‘360 degree marketing’ is the term given to the media environment that sees young children exposed to multiple forms of advertising for high calorie foods and consumable toys, clothing and products [1]. This term describes current marketing communication strategies through which children are targeted via multiple media, including radio, TV and social media, food packaging, point of sale advertising, direct mail, and blanket coverage of prime sites in public spaces. Traditionally, the impact of ‘360 degree marketing’ on young children is studied in diverse fields of research. For example, obesity research considers the influence of advertising on children’s food choices and the role of media viewing on children’s levels of physical activity [2,3]. Media research canvasses the types of media young children consume, the range of technologies they use to watch media, and the number of hours they typically spend engaged with media [4]. Environmental education examines the extent to which children’s digitally mediated experiences influence the quality of children’s active outdoor play, affinity with nature and children’s consciousness of the sustainability consequences associated with their clothing and toy preferences [5]. Meanwhile in early childhood education and early primary/elementary school settings, educators increasingly bemoan the extent to which ‘360 degree marketing’ influences young children’s play, the type of foods they bring to their centres and the range of clothing and toys in which they are interested [6].

An important issue for educators attempting to respond to this problem is the lack of research conducted from an integrated perspective into the best way to respond to young children’s exposure to saturation marketing via the early childhood curriculum. An integrated systems approach is needed to incorporate these important aspects, which are influencing children’s education and health and well-being. Encouraging children to take a holistic approach and enabling them to understand the consequences of their actions provides them with skills in the future to best handle unanticipated consequences.

Current contexts for children’s development in contemporary industrialised societies have been described by some social commenters as ‘toxic’ [7] promoting the phenomena of ‘nature-deficit’ [8] and ‘ecological illiteracy’ [9] among young children. These beliefs stem from the rapid adoption of digital technologies in society more broadly [10], and are aligned with advances in marketing techniques to young children that interface children’s affective engagement with popular culture characters with their engagements with digital media [11]. Young children are now commonly described as using a broad range of technologies to access and watch digital media that both promote particular characters [12], and expose children to advertising for high calorie foods, toys and clothing that have significant ‘cradle to grave’ impact on the environment [6,13,14].

In addition, research shows that increased digital media viewing is associated with reduced physical activity and levels of active play [15]. The combination of increased dietary intake of high calorie foods and reduced active play has had a profound impact on children’s weight gain across Australia, and other developed countries. Obesity in early childhood is currently recognised as a significant concern and one that is associated with children’s self-esteem placing them at later risk of depression [16]. Meanwhile, education for sustainability has become increasingly important for young children [17,18]. This has involved encouraging children to participate in green activities, such as gardening and composting food [19]. However, a more critical perspective in which children are encouraged to think about the environmental consequences of their consumer behaviour in light of their food and toy choices is yet to feature in early childhood education [12].

Sociocultural accounts of children’s learning and development promote strong connections between children’s home and community experiences and the provision of learning activities in early childhood education. This perspective is recognised in the notion of ‘funds of knowledge’ [20], where it is argued that curricula should be derived from children’s home and family interests and developed by educators as contextual responses to children’s cultural experiences [21]. This means that curricula driven by children, educators and families are recognised in early childhood education as more likely to achieve learning outcomes than imposed interventions. In the past, obesity prevention research directed towards young children has neglected to account for this perspective on teaching and learning and has been directed by the researchers and hence the research program instead [22]. We have developed a pedagogical communication strategy, using a ‘funds of knowledge’ perspective that acknowledges children’s likely engagement with digital media as a form of cultural experience; the strategy was developed in close consultation with children, families, and educators. Utilising the play experiences children have in their homes and communities are explored in the early childhood classroom. Educators may have further exposure to educational opportunities by asking children why they like to play with specific characters. A popular character for preschool children currently is Ben 10™; children are exposed to Ben 10™ through various digital mediums, which are then reinforced through marketing of Ben 10™ products such as clothes, toys and food. Consequently, the strategy is designed to enable educators to use their understandings of children’s play interests (such as wanting to play Ben10™) as the basis of the curriculum interventions.

The design focus on identifying children’s knowledge about healthy eating, active play, and sustainability, therefore, rests on a conceptual framework that strongly aligns with existing teaching and learning processes in early childhood education.

In early childhood education, the release of the Australian Early Years Learning Framework (EYLF) in 2009 [23] saw a focus on children’s wellbeing in terms of healthy eating and some awareness of environmental education in terms of children’s engagement with the natural world included in the early childhood curriculum. However, an integrated approach towards helping young children respond to the significant pressures of ‘360 degree marketing’ [1] on their food choices, levels of active play, and sustainability consciousness via the early childhood curriculum is lacking. The present study takes a targeted approach to the Ben10™ problem by providing educators with a pedagogical communication strategy for integrating healthy eating, active play, and sustainability consciousness in the early childhood curriculum. Because the pedagogical communication strategy is aligned with the Australian EYLF educators are able to use it in order to develop curriculum interventions that integrate obesity prevention, digital media and sustainability education experiences for young children; this is in direct contrast to previous approaches to health and sustainability education in early childhood, which has tended to focus on these issues separately. In addition, our proposed research accords with the *Australian Curriculum: Health and Physical Education* that requires teachers to provide opportunities for children and adolescents to adopt lifelong healthy, active living strategies that empower them to enhance their own and others’ health and wellbeing in varied and changing contexts [24]. Hence, the overall goal of the current study is to conduct a cluster randomised trial to evaluate the efficacy of the curriculum interventions that educators design when using the pedagogical communication strategy on children’s knowledge about healthy eating, active play and the sustainability consequences of their toy food and toy selections.

## Methods/Design

### Overall study design

This study is a cluster-randomised trial with pre-school classes of 4 to 5 year-old children randomly allocated to either an intervention or control group and will be conducted and reported in line with CONSORT recommendations. Baseline assessment of study variables will occur prior to implementation of the intervention. Follow up assessments will take place immediately following and 6 months post completion of the intervention strategy. The intervention group children will receive the curriculum interventions that their educators develop. The wait-list control group children will receive ‘usual care’, that is, their educator’s usual teaching approaches. The project has been approved by the Victorian Department of Education and Early Childhood Development and has received ethics approval from the Deakin University, Australian Catholic University and Southern Cross University Human Research Ethics Committee (DHREC 2013–220, 2014 39 V, and ECN-14-001, respectively).

### Hypotheses

In comparison to the control group, at the completion of the intervention and at 6 months post intervention there will be a significantly greater proportion of children in the intervention group who will: (1) show significant improvements in their knowledge about healthy eating, active play and the sustainability consequences of their food and toy selections; (2) demonstrate greater consumption of fruit and vegetables, and a decrease in consumption of high fat, and energy dense snack foods, especially those that are pre-packaged and marketed with popular media characters; and (3) demonstrate greater increases in active play and decreases in time spent in sedentary behaviours, specifically digital media viewing.

### Participants

The participants will be 300, 4–5 year old children, who attend preschool/childcare, their educators, and their English-speaking parents. The children will be attending early learning settings in the year prior to school and attending the first year of primary/elementary school in the following year.

### Recruitment strategy

The study will consist of at least 30 of the 68 available preschools (from Early Childhood Services Management (ECMS), Victoria) and aims to retain a total of at least 300, 4–5 year old children, who attend preschool together with their English speaking parents (because the program is only offered in English); the children will be in their final year of preschool. With a likely quota of 10 participants per preschool, 30 preschools (15 matched pairs) are required, 15 randomized to each arm of the study. Our formative work indicated a potential 11% attrition rate. Making a prudent allowance for attrition of up to 20%, 360 4–5 year old children and their parents will therefore be recruited and the adjusted number of preschools per study arm is likely to be 18 (i.e. a total of 36 kindergartens in 18 pairs).

## Procedure

### The Teacher Intervention

Teachers participating in the intervention group will be provided with a copy of the pedagogical communication strategy and asked to develop a curriculum intervention that integrates content knowledge about healthy eating, active play and sustainability consciousness. They will then attend a professional learning session to orientate them to the project. This session will be hosted by the Chief Investigators. Each teacher’s curriculum intervention will be workshopped to ensure they have included the following components: 1) implementing the interventions over 1–2 days across a period of 3–4 weeks to build a solid portfolio of experiences and strong base for children’s discussions; 2) implementing the interventions in the morning when the children are most cognitively alert; 3) combining both whole group and small group experiences and discussions; 4) using ‘real world’ props/resources, such as cereal boxes, McDonald’s Happy Meal™ boxes and toys and merchandise; and 5) maintaining assessment records of children’s learning using Learning Stories [25], observation and documentation. Teachers will be provided with an ‘*Intervention Implementation Checklist’* and asked to record all components/elements associated with their curriculum interventions including: date, time, and duration of the intervention; the number of times the intervention or iterations of the intervention were implemented; Early Years Learning Framework Learning Outcomes aligned with the intervention; complete description of the intervention (including any resources/props used) and examples of any approaches to assessing children’s learning used in relation to the intervention. A booster session will be conducted 6 weeks after teachers implement their curriculum interventions whereby children will be exposed to an abridged version of the intervention.

### Wait-list control group

The wait-list control group children will receive ‘usual care’, that is, their usual teaching and learning experiences as designed by participating educators. Qualitative and quantitative measures will be administered at the same time points as the intervention group. The teachers and children in this group will be offered the intervention at 7 months post baseline assessment.

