### Measures

At recruitment, parents will be asked to complete an informed consent form confirming their participation in the study. The following measures will be administered at baseline, the end of the intervention and 6 months post intervention.

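### The wait-list offer is dated from baseline and the last control assessment from completion of the intervention, and nothing stops the offer from coming first

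*Protocol article*

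**What the plan says.** The Wait-list control group section dates the crossover from baseline: its teachers and children will be "offered the intervention at 7 months post baseline assessment". The same section ties control measurement to the other arm: "Qualitative and quantitative measures will be administered at the same time points as the intervention group".

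Those time points run from a different origin. Overall study design says: "Follow up assessments will take place immediately following and 6 months post completion of the intervention strategy". Measures repeats the three occasions: "The following measures will be administered at baseline, the end of the intervention and 6 months post intervention".

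The Teacher Intervention section describes delivery as "implementing the interventions over 1–2 days across a period of 3–4 weeks", and adds: "A booster session will be conducted 6 weeks after teachers implement their curriculum interventions". It does not say whether the booster counts towards completion, or whether its 6 weeks run from the first or the last day of delivery.

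For the period before delivery, Overall study design says only: "Baseline assessment of study variables will occur prior to implementation of the intervention". Under Analyses, the parents' baseline data are locked before allocation. Under The Teacher Intervention, teachers in the intervention arm receive the strategy, draft a curriculum, attend an orientation session and have the draft workshopped. No duration is given for any of this. No section makes the offer to controls conditional on their last assessment.

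**The concern.** Two dates that must fall in a fixed order are counted from different starting points. The offer is a calendar date after baseline. The last control assessment moves with the date on which the intervention arm finishes. Any delay in starting or finishing pushes the assessment back and leaves the offer where it is.

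All three hypotheses are stated at two times, completion and 6 months later, and the first concerns the primary knowledge outcome. If control children have begun or finished the curriculum before the later measurement, that comparison no longer sets taught children against untaught ones, and the controls would be the more recently taught group. No analysis can restore an untreated control group afterwards.

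**Working it through.** **Inputs.** Offer to controls: 7 months after baseline (Wait-list control group). Last assessment: 6 months after completion (Overall study design, Measures). Delivery *d*: 3 or 4 weeks, that is 21 or 28 days (The Teacher Intervention). Booster: 6 weeks, 42 days (same section). Gap *g* from baseline to the first lesson in the intervention arm: not stated, so a range is assumed. One month is taken as 365.25/12 = 30.44 days, so 6 months = 182.6 days and 7 months = 213.1 days.

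**Step 1: reproduce the 7 months.** Last follow-up = *g* + *d* + 182.6 days. With *g* = 0:
- 3 weeks: 21 + 182.6 = 203.6 days = 6.69 months
- 4 weeks: 28 + 182.6 = 210.6 days = 6.92 months

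So 7 months matches about one month of delivery plus six months of follow-up, with nothing allowed for preparation or late visits. The margin before the offer is 9.4 days (3 weeks) or 2.4 days (4 weeks).

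**Step 2: the gap that uses up the margin.** Setting *g* + *d* + 182.6 = 213.1 gives *g* = 30.44 − *d*, which is 9.4 days for 3 weeks and 2.4 days for 4 weeks. A longer gap puts the offer before the last assessment.

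**Step 3: assumed gaps, clock starting at the end of main delivery.**

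| Gap *g* | Last follow-up, months from baseline | Days relative to the offer |
|---|---|---|
| 0 | 6.69–6.92 | 9.4 to 2.4 before |
| 2 weeks | 7.15–7.38 | 4.6 to 11.6 after |
| 4 weeks | 7.61–7.84 | 18.6 to 25.6 after |
| 8 weeks | 8.53–8.76 | 46.6 to 53.6 after |

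**Step 4: booster counted towards completion, *g* = 0.**
- 42 days from the start of delivery: 42 + 182.6 = 224.6 days = 7.38 months, 11.6 days after the offer
- 42 days from the end of delivery: 63 or 70 + 182.6 = 245.6 or 252.6 days = 8.07 or 8.30 months, 32.6 or 39.6 days after the offer

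**Step 5: from offer to teaching.** Let *c* be the days from the offer to the first lesson in a control preschool. On the main-delivery clock, control children are taught before their last assessment when *g* + *d* + 182.6 > 213.1 + *c*, that is when *g* − *c* > 30.44 − *d*. If *c* = *g*, the lags cancel and the assessment comes first by 9.4 or 2.4 days. If the intervention arm's lag is longer than the controls' by more than that, teaching comes first. With the booster counted and *c* = *g*, control teaching starts 11.6 days (6 weeks from the start) or 32.6–39.6 days (6 weeks from the end) before the last assessment. In the latter case a delivery of 21–28 days could be over by then.

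**The case against.** The strongest reply is that an offer is not exposure. Control teachers would presumably need similar time to draft and workshop a curriculum. If that time equals the gap in the intervention arm, it cancels (step 5), and on the main-delivery clock control children are still measured 2–9 days before teaching starts. This stands, and it is why exposure is a risk and not a certainty. It does not remove the risk: the article does not say that the lags are equal, allocation falls only in the intervention arm's gap, and a margin of 2–9 days is thin for assessments planned in about 36 preschools.

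Second, the gap might be short. Only the parents' data must precede allocation; child interviews could take place after teacher preparation, just before the first lesson. That is possible, so a zero gap cannot be excluded for the child measures. It is less likely for the parent questionnaire, which precedes allocation and therefore any preparation that follows it.

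Third, counting the booster as completion is not the natural reading, because it would delay the assessment meant to follow the intervention immediately. This is fair. The text does not settle it, however, and the concern does not depend on it.

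Fourth, a full protocol may hold the site schedule. But the article itself fixes both dates, and they agree only if almost no time passes between baseline and the first lesson.

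A reader might go further and infer that the stated durations force the follow-up past 7 months, or that the 6-month difference will vanish or reverse. The documents do not support either. Delivery plus 6 months alone ends just before 7 months, and a lost or reversed difference is a worst case in which controls finish the curriculum first.

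**Conclusion.** The point holds as an unsafe timing rule. On the stated durations alone the last control assessment precedes the offer by 2–9 days. It falls after the offer once the baseline-to-start gap exceeds about 9 days (3-week delivery) or 2 days (4-week delivery), or if the booster counts towards completion. The dated examples rest on assumed gaps of 2, 4 and 8 weeks; the article gives none.

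Whether control children are actually taught before measurement depends on how long their teachers take to prepare, which is also not stated. If it happens, the likely effect is bias towards no difference at 6 months, of a size that cannot be calculated from the document. The comparison at the end of the intervention is not affected.

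**What to change.** Reconcile Overall study design, The Teacher Intervention, Wait-list control group and Measures. Replace the fixed 7-month date with an event rule: a control preschool is offered the curriculum only after its own 6-month child interviews and parent questionnaires are complete. State whether the 6-month clock starts at the end of main delivery or at the booster.

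The cost is wording and scheduling. Some control preschools would receive the offer some weeks later, and some control children may have left preschool by then.
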